## Abstract

**Background:**

People with severe mental illness (SMI) face a significantly higher risk of victimization than the general population. Beyond physical harm, such experiences can severely impact mental health and recovery processes. Empirical research on violence prevalence among people with SMI in Germany is limited, with little understanding of mechanisms, the impact of gender, and the victim-perpetrator overlap. In order to develop successful prevention strategies against victimization, a comprehensive understanding of the complex phenomenon of victimization is needed. The study aims to develop a comprehensive understanding of the biographical, socio-cultural and institutional context factors related to experiences of violence, as well as to identify barriers to addressing such experiences within mental health settings.

**Methods:**

In a mixed-method study incorporating a quantitative survey and qualitative instruments, we investigate the prevalence of violence, including both victimization and perpetration, among people with SMI. Our study includes the following: (1) In a sample (n=500) of people with SMI, treated in inpatient and outpatient mental health settings, we will investigate the prevalence of victimization and violent behavior, (self-)stigmatization, and barriers for disclosure of experiences of violence within mental health settings. Data will be obtained from samples at seven psychiatric hospitals with mandatory care on a fixed day. For comparisons with the general population, we use an online sample (n=1000). (2) Based on this, we conduct qualitative interviews with a subsample of people with SMI (n=30) who reported experiences of violence. Using biographic-narrative interviews, we focus on the biographical and socio-cultural context (3). In addition, we use qualitative and quantitative measures to investigate mental health professionals’ experiences, institutional factors, and strategies to deal with mental health service users’ violence experiences.

**Discussion:**

Developing interventions to prevent and reduce victimization requires a systematic assessment of mental health service users’ violence experiences and a comprehensive understanding of the biographical, socio-cultural, and institutional factors. Our study aims to contribute fundamentally to a deeper understanding of violence experiences in Germany, thereby providing the basis for the development of targeted interventions to improve the awareness and the handling of violence experiences among a specific vulnerable group.

**Trial registration:**

This study is registered in the German Clinical Trial Register (DRKS) and the WHO International Clinical Trials Registry Platform (ICTRP) under registration number DRKS00032041 (Date of registration July 2023).

## Introduction

Compared to general population data, people with severe mental illness (SMI) are more likely to experience physical and/or sexual violence (1, 2). A meta-analysis indicated a 5-fold relative odds for any physical violence in people with SMI compared to those without SMI (2). Regarding the prevalence and risk of sexual violence, a recent meta-analysis revealed high pooled prevalence estimates and increased odds in male and female psychiatric service users compared to non-psychiatric service users (1). Violence experiences cause not only physical harm but can also have detrimental effects on mental health, predisposing individuals to the onset and severity of psychosis (3, 4) and leading to self-stigmatization (5). Experiences of violence are often shaped by biographical trajectories, unfolding across the life course. While early victimization increases the risk of developing mental health problems later in life, the likelihood of further victimization rises after the onset of mental illness. A Danish cohort study, including more than 2 million individuals, observed an increase in the incidence of victimization following the onset of mental illness (6). Studies on victimization among people with SMI have identified a number of risk factors with mixed findings on the role of psychopathology, cognitive deficits, diagnoses and substance (mis)use (7–10). Social risk factors include unemployment and homelessness (9), poverty (11) and social exclusion (12).

Regarding gender, evidence suggests that women and men with SMI experience similarly high rates of physical violence (2). This is noteworthy, as population data typically show higher prevalences of physical victimization among men (13), indicating that the gender difference observed in the general population is reduced among people with SMI (2). For sexual violence, while women with SMI experience higher rates of victimization than men with SMI, the gender gap is narrower than in the general population (2). Overall, both women and men with SMI face markedly elevated risks of violence compared to the general population (2).

Relative incidence rates confirm women’s particular vulnerability to violence: With the onset of a mental illness, women’s risk of experiencing violence increases by 2.7 times (compared to a 1.8 times enhanced risk in men) (6). Women with SMI also face a significantly heightened risk of sexual violence: Compared to women in the general population, they are nearly ten times more likely to be victims of sexual violence (2). Studies which systematically address the role of gender for experiences of violence among individuals with SMI are still rare.

Sociocultural factors play a crucial role in shaping the vulnerability and experiences of individuals with SMI in the context of violence. Ethnicity and migration background are relevant when investigating violence experiences among individuals with SMI. Refugees and asylum seekers have been found to frequently experience violence and related health problems, with elevated rates of both physical and sexual victimization as well as mental health conditions (14). Thus, racial and ethnical marginalization needs to be considered as a potential risk factor for (re)victimization (15). In addition, prevailing societal and professional perceptions of mental illness may also play a role in violence experiences among this group. The psychiatric discourse on violence is often characterized by notions of higher prevalence of perpetration than victimization and by notions of a perpetrator-victim dichotomy, implying that individuals are either perpetrators or victims. However, a recent systematic review on interpersonal violence perpetration and victimization risk within single study cohorts provided evidence for higher rates of victimization than perpetration among both individuals with SMI and those in the general population, and for higher rates of both victimization and perpetration among individuals with SMI compared to the general population (16). Empirical studies indicate an overlap between victimization and perpetration. A secondary analysis of five U.S. studies (total sample n=4474) revealed that, compared to individuals who only experience violence (13.3%) or only perpetrate violence (6.3%), those who both experienced and perpetrated violence (17.6%) were more prevalent (17). This aligns with the results of a Swedish registry study, which found a significantly higher risk of combined victimization and perpetration among individuals with a psychiatric diagnosis compared to isolated victim or perpetrator experiences (7). According to a meta-analysis of studies on violence and mental illness, previous experiences of violence increased the risk of perpetration by a factor of 6 (18). A prospective study demonstrated that experiences of violence within the past six months significantly increased the risk of perpetrating violence in the following year, outweighing other risk factors (19). To date, beyond prevalence rates, little is known about the forms and mechanisms of overlapping perpetrator-victim perspectives among individuals with SMI.

Mental health professionals are in a central position to identify victimization among service users and to provide adequate support. However, despite the strong evidence for the increased risk among people with SMI and the detrimental effects of victimization for individuals and their families (20), victimization among people with SMI is often neither systematically recorded nor considered in mental health care (21–23). Victims of violence identify key barriers to disclosure, including feelings of shame and guilt, delayed realization of the violence, fear of subsequent violence, and inappropriate reactions to the disclosure (24). Mental health professionals report feeling overwhelmed and uncertain in recognizing and dealing with experiences of violence, fearing negative consequences for the victims, or refer to practical barriers such as a lack of time (24). In an Australian study, professionals were found to have varying responses to disclosures of sexual assaults, including disparaging views that led to minimizing, ignoring, or blaming the disclosures, and while some acknowledged the prevalence of sexual violence, they felt ill-equipped to respond appropriately (25). The lack of mental health professionals’ engagement with the phenomenon of service users’ victimization brings about three significant problems: First, it impedes the early detection and addressing of experiences of violence in medical history taking and therapy, which is crucial for trauma-therapeutic interventions and support, e.g. connecting to specialized services (26). Second, there is a risk for re-traumatization that can occur in inpatient settings, particularly in regard with coercive measures. Seclusion and/or restraint can have deleterious physical and psychological consequences including post-traumatic stress disorders particularly for people with previous experiences of victimization (26). However, studies on re-traumatizing experiences during inpatient treatment are scarce, and the role of gender remains widely unclear. Third, the lack of awareness and engagement of mental health service providers hinders the development of structural measures to prevent and reduce the risk of people with SMI becoming victims of violence within and without mental health settings. As the outlined background on victimization of people with SMI demonstrates, developing effective measures to prevent victimization requires a comprehensive understanding of the complex and multifaceted underlying mechanisms of violence, as well as an understanding of the factors influencing the disclosure of such experiences in mental health settings.

According to Thom et al. (27) around 37.9% of the population are affected by a mental illness. Recent reviews emphasize that despite evidence of elevated victimization rates among people with SMI, representative prevalence studies that allow for cross-country comparisons and population-based estimates in Germany remain scarce (28). Moreover, more research is needed to provide a comprehensive picture of the risk variables influencing victimization experiences (29). Taken together, these gaps highlight the need for further research that combines representative prevalence data with an analysis of social, biographical and institutional factors to provide a more comprehensive understanding of victimization among people with SMI.

## Methods

### Study aim

The study aims to provide a comprehensive analysis of violence experiences including victimization and perpetration amongst people with SMI including:

Frequencies, forms, contexts, and disclosure of physical and sexual violence experiences among people with SMI in Germany, including overlaps between victimization and perpetration.Impact of gender, biographical and socio-cultural factors correlations; and the subjective meanings and attributes of violence experiences.Mental health professionals’ views on violence experiences among mental health service users.

### Epistemological and methodological framework of the study

This mixed-method study is positioned at the intersection of sociological violence research, social psychiatry, and gender studies. Social psychiatry emphasizes the social, biographical, and cultural influences on the development, course, and management of mental illness, and highlights the reciprocal relationships between subjects and their environments (30). In turn, sociological violence research conceptualizes violence as an intentional act of power embedded in social orders and shaped by situational and contextual conditions (31). Following Popitz’s definition of violence as an intentional act leading to physical harm (32), the study focuses on physical violence (e.g., hitting, kicking, robbery, armed assault) and sexual violence (e.g., harassment, attempted rape), including domestic and partner violence. Methodologically, the study combines context-centered approaches, which examine macro-social and cultural conditions (e.g., poverty, norms, inequality), with situation-centered approaches, which reconstruct interactions and subjective interpretations of violence on the micro-sociological level. Particular emphasis is placed on the biographical embedding of violent experiences, recognizing their temporal structuring and dynamic unfolding across the life course. By linking social, institutional, and biographical factors, this design allows us to explore how prior experiences, life trajectories, and environmental contexts intersect to shape patterns of victimization among people with severe mental illness. From a gender perspective, the framework draws on feminist and sociological theories that interpret male violence against women as an expression of dominance, while situating violence among men within the construction and negotiation of hegemonic masculinities (33). This dual lens enables the analysis of both hetero- and homosocial dimensions of violence. At the same time, the framework transcends dichotomous attributions of (male) perpetrators and (female) victims by addressing victim-offender overlaps and the situational as well as biographical dynamics that link victimization and violent behavior. In this way, mechanisms of inversion between victim and perpetrator roles can be identified, and the impact of socialization processes or continuous exposure to violence on trajectories of vulnerability and violent behavior can be systematically addressed.

### Study design

We conduct a cross-sectional mixed-method study consisting of three subprojects. The mixed-method-design will be realized by combining quantitative survey data (subproject 1) and subsequent qualitative narrative-biographical interviews (subproject 2) in line with an Explanatory Sequential Design (34). Qualitative focus groups, interviews and subsequent survey data (subproject 3) will be combined according to the Exploratory Sequential Design (34).

Subproject 1: Quantitative cross-sectional survey with mental health service users.We will conduct a quantitative cross-sectional study involving 500 people with SMI through a key date survey conducted in various psychiatric clinics. Additionally, a representative sample of 1000 individuals from the general population will be surveyed by USUMA, a German market and social research institute.Subproject 2: Qualitative study with mental health service users.

We will conduct a qualitative study using narrative-biographical interviews data involving a subsample of approximately 30–40 people with SMI from subproject 1.

Subproject 3: Qualitative study and quantitative survey with mental health professionals.

In a first step, we will collect qualitative data through approximately 30 semi-structured interviews and four focus groups with mental health professionals. In a second step, we collect quantitative data from approximately 100 mental health professionals.

### Participants and eligibility criteria

The standardized survey of subproject 1 includes people with SMI of legal age (18+ in Germany) who are undergoing treatment in one of the participating clinics at the time of recruitment. The term “people with SMI” refers to individuals diagnosed with mental illness that significantly impair their ability to function in daily life. These conditions often include disorders such as schizophrenia, bipolar disorder, or severe major depression, and typically require (long-term) treatment and support (35). For our study, we operationalize the term “people with SMI” based on the indication for psychiatric hospitalization, as well as outpatient treatment in a psychiatric hospital or outpatient service, which is considered an indicator of “severe mental illness”. Synonymously we use the term “mental health service user”. Exclusion criteria include language barriers and cognitive deficits, such as dementia or intellectual disabilities.

The qualitative study of subproject 2 includes persons of legal age who took part in the standardized survey in subproject 1. The selection of participants is based on the extent of violence experienced as indicated in the standardized questionnaire. Participants who report experiences of physical or sexual violence will be considered eligible for the qualitative interviews. The phrase “beyond a cut-off” refers to the self-reported occurrence of at least one experience of physical or sexual violence in the questionnaire. Final selection will additionally consider the forms of violence reported and sociodemographic characteristics in order to ensure heterogeneity of cases.

Individuals who meet these criteria and agree to participate in a narrative-biographical interview will be included. In subproject 3, mental health professionals from the fields of nursing, psychology, social work, and medicine who are employed at one of the participating clinics will be recruited for the qualitative interviews and focus groups, and for the subsequent quantitative survey.

### Participant timeline

The recruitment period for participants in subproject 1 has started in January 2024 and will continue until August 2025. At the time of submitting this protocol, 250 participants have been included in the study. The recruitment of participants for the narrative-biographical interviews in subproject 2 has started in August 2024, with the interviews set to be conducted until August 2025. Participants for the qualitative interviews in subproject 3 have been recruited since March 2024, with the recruitment period scheduled to end in February 2025. At the time of the submission of this protocol, (n=29) interviews have been conducted. Participants for the focus groups in subproject 3 are scheduled to begin in December 2024 and will be conducted until June 2025. Participants for the questionnaire survey in subproject 3 will be included in the study from October to December 2025.

### Outcomes

#### Subproject 1 (quantitative cross-sectional survey with mental health service users)

The primary outcome of subproject 1 is the frequency of violence experiences among people with SMI, both as victims and perpetrators, compared to a control group from the general population. The study examines correlates and contextual factors of violence, such as gender, socioeconomic status, social support, coping resources, and psychopathology. The secondary outcomes include the impact of internalized stigmatizing beliefs among people with SMI, especially in relation to violence experiences. Furthermore, barriers of disclosure will be assessed, focusing in whom these experiences have been communicated to, why or why not, and whether they have been incorporated into treatment if reported in a clinical setting.

#### Subproject 2 (qualitative study with mental health service users)

The aim of subproject 2 is to gain a deeper understanding of the subjective meaning of violence experiences from a biographical perspective with a focus on gender and victim-perpetrator-dynamics. We are interested in both the processual nature of violence within the biographical context and the biographical processes as a result of violence experiences. Particular attention will be paid to biographical continuities, breaks, and changes in the narratives of violence experiences, including the phenomenon of serial victimization and re-victimization both within and outside of mental health services. Furthermore, we will pay particular attention to normative expectations, perceptions of stigma in relation to violence experiences, and the interrelation between stigmatization and the disclosure of violence experiences.

#### Subproject 3 (qualitative study and quantitative survey with mental health professionals)

The aim of subproject 3 is to analyze the experiences and attitudes of mental health professionals regarding violence experiences among mental health service users and to compare these views with those of the service users themselves concerning their experiences of violence. We build on existing findings related to the barriers and facilitating factors identified by professionals concerning the disclosure of experiences of violence. We are particularly interested in the individual (experiences, attitudes) and contextual factors (setting) from the professionals’ perspective that can influence disclosure within the context of psychiatric treatment, with a specific focus on the role of gender in dealing with the service users’ experiences of violence.

### Recruitment and sample size calculation

#### Subproject 1 (quantitative cross-sectional survey with mental health service users)

Focusing on people in psychiatric treatment allows us to survey a representative sample of a defined population. This group represents those with immediate access to therapeutic interventions, and therefore to potentially address experiences of violence. A sufficiently large sample is targeted to enable adequate analyses of different context factors. The sample size of n=500 is chosen to enable the most precise estimation possible of the prevalence of violence experiences.

For statistical power analysis regarding the sample size in subproject one, considering the overall exploratory nature of this study, the variety and theoretical parity of the variables of interest (no primary predictor), and the scarcity of published data that could guide a strict *a priori* power analysis, we liberally set the sample size to 500 or 100 per clinic, respectively. This sample size is sufficient to detect group differences of medium to large effect sizes with a maximum error rate of 5% for both Type I (alpha) and Type II (beta) errors. We illustrate this with the analysis of clinic-level effects using G*Power 3.1.9.7 (36). Based on 500 data points, global parametric comparisons for independent groups can detect site effects on metric variables such as respondent’s age down to f=0.20 with a power of at least 95% (one-way ANOVA with fixed effects, 5 equally-sized groups). This corresponds to site effects on ordinal (e.g. socioeconomic status), nominal (e.g. marital status), or binary variables (e.g. gender) of w≥0.20 (Chi^2^-distribution based tests, df=4). For comparison, a previous study by Johnson et al. (2015) (37) found only a marginal effect of gender on participant status as victim, perpetrator or victim/perpetrator compared to people who did not experience violence (w=0.06, p<0.01). However, comparability of this study’s sample with our target population is strongly limited, as men and people with schizophrenia were overrepresented (59.8% and 63.4%, respectively). For our study, we expect considerably more women than men in psychotherapeutic services (38) and lower rates of schizophrenia, given a prevalence rate of less than 1% in Germany (27).

Participants will be recruited at the following cooperating hospitals: Clinic and Polyclinic for Psychiatry and Psychotherapy, University Hospital of Leipzig (urban area) (n=100); “Helios Park” - Hospital Leipzig (urban area) (n=100); District Hospital Guenzburg (small town/rural area) (n=100); Specialized Hospital Bethanien Hochweitzschen (rural area) (n=100); Helios Hanseatic Hospital Stralsund (rural area) (n=100). Since violence is a taboo topic, we expect that many people may not want to participate in our study. In order to still obtain a sufficiently large sample size to calculate the aforementioned statistical parameters, we have additionally collaborated with the following two clinics: The Clinic for Psychosomatic Medicine and Psychotherapy at the University Hospital Ulm (urban area). Further, we cooperate with the Clinic for Psychiatry, Psychotherapy and Psychosomatics, Saxon Hospital Altscherbitz, Germany (outskirt of Leipzig). A cooperation has been requested with the Clinic for Psychiatry and Psychosomatics at the District Hospital and the University of Augsburg (urban area).

On a specified key date, the project staff will approach all patients who are receiving partial or full inpatient treatment. For practical reasons, different key dates will be chosen for various treatment units (wards, outpatient clinics). Recruitment will continue in each clinic until the target sample size is reached. Inclusion criteria were legal age (18 years) and German language skills. Exclusion criteria were dementia, intellectual impairment, current psychotic symptoms, and if the person was in isolation or fixation. All patients that meet the inclusion criteria and don’t need to be excluded for above mentioned reasons will be asked if they would agree to fill out the questionnaire. They will be handed the participants information and fill out informed consent (see section “Ethics”).

Furthermore, we will recruit a general population sample (n=1000) through an online survey conducted by USUMA.

The rationale for including a comparison group from the general population is to contextualize prevalence estimates observed among people with SMI and to determine whether observed rates exceed background population levels. The general population sample is recruited via an online survey conducted by USUMA, which enables access to a large and heterogeneous sample and allows quota sampling based on key sociodemographic characteristics (e.g., age, gender, and region), thereby supporting structural comparability between groups.

People with SMI are recruited in psychiatric services and complete the same standardized self-report measures on-site (paper-pencil or tablet-based). Although both samples rely on identical instruments, differences in recruitment context and survey mode (online vs. clinical setting) may introduce potential mode effects, which will be considered as a potential limitation when interpreting group differences in prevalence.

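### The clinic survey is called representative, but the steps taken against expected topic-driven refusal protect the sample size and not representativeness, so the prevalence is exposed to non-response bias

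*Protocol article*

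**What the plan says.** All of the following comes from the protocol article; unless noted, it stands under Recruitment and sample size calculation, Subproject 1.

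- **The claim:** "Focusing on people in psychiatric treatment allows us to survey a representative sample of a defined population".
- **The purpose of the sample size:** "The sample size of n=500 is chosen to enable the most precise estimation possible of the prevalence of violence experiences". Under Outcomes, this is also the main target of the subproject: "The primary outcome of subproject 1 is the frequency of violence experiences among people with SMI, both as victims and perpetrators".
- **The approach:** "On a specified key date, the project staff will approach all patients who are receiving partial or full inpatient treatment". Key dates differ between treatment units for practical reasons.
- **The exclusions:** "Exclusion criteria were dementia, intellectual impairment, current psychotic symptoms, and if the person was in isolation or fixation".
- **The expected refusal:** "Since violence is a taboo topic, we expect that many people may not want to participate in our study". No expected response rate is given.
- **The response to it:** "In order to still obtain a sufficiently large sample size to calculate the aforementioned statistical parameters, we have additionally collaborated with the following two clinics". Cooperation with a third clinic has been requested. Five clinics are listed with n=100 each; the added clinics carry no number.
- **The end of recruitment:** "Recruitment will continue in each clinic until the target sample size is reached".

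The section Promotion of study participation describes information meetings, face-to-face introduction on the wards, a flyer and staff support during completion. For the comparison with the online sample, the limitation named is a possible mode effect from recruitment context and survey mode. Non-response is not named there.

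**The concern.** Approaching everyone present on a key date gives good coverage of the eligible patients. The participants represent that group only if those who decline resemble those who agree with respect to violence. The protocol gives reasons to doubt this:

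- It expects refusal because of the topic.
- Its Introduction lists shame, guilt and fear of further violence among the reasons why victims do not disclose.
- The Informed consents section has the aims explained before consent, so patients can decline because of the subject.

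The planned response treats this as a shortage of numbers. More clinics and continued recruitment reduce sampling error, but they leave the difference between participants and refusers where it was.

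At stake is the primary estimate and its comparison with the general population. The Introduction presents representative German prevalence data as scarce, so readers are likely to rely on the label. The secondary outcome on barriers to disclosure is exposed to the same selection, since those least willing to disclose may also be those least willing to take part.

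**Working it through.** **1. The plan's own figure.** The stated power is at least 95% for site effects with N=500, five equal groups and alpha 0.05.

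- ANOVA, f=0.20: noncentrality 500 × 0.20² = 20, df 4 and 495, power 96.2%.
- Chi-square, w=0.20, df 4: noncentrality 500 × 0.20² = 20, power 96.4%.

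The figure reproduces. It concerns differences between sites and has no bearing on who takes part.

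**2. Sampling precision at n=500.** The 95% half-width under simple random sampling is 1.96 × √(p(1−p)/500).

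| Prevalence p | Half-width (points) |
|---|---|
| 10% | 2.6 |
| 20% | 3.5 |
| 30% | 4.0 |
| 50% | 4.4 |

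At p=50% the full interval is 2 × 4.4 = 8.8 points wide.

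**3. Bias from refusal.** Bias = (1 − response rate) × (prevalence in responders − prevalence in non-responders). The documents give neither input, so the values below are assumptions. The table gives the absolute size; the sign is that of the difference.

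| Response rate | Difference 5 points | 10 points | 15 points |
|---|---|---|---|
| 40% | 0.60 × 5 = 3.0 | 6.0 | 9.0 |
| 50% | 0.50 × 5 = 2.5 | 5.0 | 7.5 |
| 70% | 0.30 × 5 = 1.5 | 3.0 | 4.5 |

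The sample size does not appear in this formula. At a given response rate and difference, reaching 500 through additional clinics narrows the interval and leaves the bias unchanged.

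**4. The same question by participation ratio.** Let k be the participation rate of patients with violence experience divided by that of patients without. The observed prevalence is then pk/(pk + 1 − p). Again k and p are assumed.

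- p=20%, k=0.8: 0.16/0.96 = 16.7%, a shift of −3.3 points.
- p=50%, k=1.25: 0.625/1.125 = 55.6%, a shift of +5.6 points.
- Over p=20 to 50%, k=0.8 or 1.25 shifts the estimate by 3.3 to 5.6 points, and the nominal 95% interval covers the true value in about 30 to 48% of samples.
- Over the same range, k=0.67 or 1.5 shifts it by 5.7 to 10 points, with coverage of 5% or less.

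The direction depends on whether k lies below or above 1. The protocol does not settle this.

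**5. Allocation.** With n=100 at each of the five listed clinics, the pooled raw prevalence is (p₁ + … + p₅)/5. The prevalence among all eligible patients of those clinics is Σ Nᵢpᵢ / Σ Nᵢ, where Nᵢ is the number of eligible patients at clinic i. The two agree if volumes are equal or if volume and prevalence are unrelated across clinics. The protocol gives no volumes, so the size of this effect cannot be computed.

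**The case against.** The strongest case on the other side has four parts.

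**The plan does more than add clinics.** A reader might infer that extra clinics are the only remedy, or that clinics are added until the number is reached. The text supports neither. The participation measures act on refusal itself, two specific clinics were added and one requested, and the sentence on continuing recruitment refers to each clinic. This stands. However, the participation measures come with no response target, and the protocol still expects many refusals.

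**Missing analysis detail is no finding.** A reader might infer that the bias will go uncorrected. This is a journal article with one short paragraph on statistics; participation logs, responder comparisons and weighting may sit in documents not shown. This also stands. The point rests on what is printed: a claim of representativeness beside an expectation of topic-driven refusal and steps that secure numbers.

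**The size is assumed.** A reader might infer that the prevalence is biased, or that the bias exceeds the width of the confidence interval. No document supports the first. On the second, the 5.0-point example exceeds the half-width of 4.4 points but not the full width of 8.8. Within the assumed range only the extreme corner, 9.0 points, passes 8.8, and the lower end of 1.5 is below even the half-width.

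**Weighting may not help.** Post-stratification by sex, age, setting and diagnosis removes only bias explained by those variables. Refusal linked to violence within a stratum remains. This is right, and it speaks against making a weighted estimate the primary one in a study that calls itself exploratory.

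The allocation point is likewise limited. The n=100 figure applies to the five listed clinics, and if the added clinics contribute to the 500, equal allocation no longer holds. It is also a separate matter from refusal.

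**Conclusion.** The concern holds as a mismatch between a stated property and the design. The protocol claims a representative sample and rests n=500 on precise estimation of the prevalence, while expecting refusal that may be related to that prevalence. Its steps protect the sample size but do not secure representativeness, and the equal numbers planned at the five listed clinics take no account of clinic volume. Approaching all eligible patients on key dates is a real strength for coverage but gives no protection against refusal.

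The prevalence is therefore exposed to non-response bias of unknown size and direction. For scale, 50% response and a 10-point difference give 5.0 points, slightly more than the sampling half-width; the range examined runs from 1.5 to 9 points. Response rates, differences and participation ratios are assumptions, and the half-width is for simple random sampling at 50% prevalence. That bias is present, or that no correction is planned anywhere, cannot be concluded from the article.

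**What to change.** 1. **Count.** On each remaining key date, tally from the ward list the patients present, excluded (by reason), refusing and participating, by sex, age band, setting and diagnosis group. For past key dates, recover the counts from hospital census data where possible.
2. **Report.** Give participation per clinic, and present the raw prevalence together with a sensitivity analysis. This should contain an estimate post-stratified to the key-date census, which also addresses clinic volume, and a bias range for outcome-linked refusal built as in the tables above with the observed response rates.
3. **Reword.** Under Recruitment and sample size calculation, replace the claim of a representative sample with *participating patients at the cooperating clinics*. Where mode effects are named as a limitation of the group comparison, name non-response beside them.

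The cost is a tally sheet per key date, some extra analysis and wider intervals for the weighted estimate. Counts for the 250 participants already included at submission may be only partly recoverable. The bias range will show how far the prevalence could move, but it cannot establish the true direction.
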